| 6 month sustained smoking abstinence               | Self reported 6 month abstinence at 12 month confirmed by exhaled CO or proxy validation (Mo 6 & 12)                                                                                                                                                                 |
| Quit attempts                                      | Cumulative number of self-reported quit attempts lasting at least 24 hours (baseline, Mo 3, 6 & 12)                                                                                                                                                                  |
| Average CPD                                        | Average number of CPD (baseline, Mo 3, 6 & 12)                                                                                                                                                                                                                       |
| Smoke exposure                                     |                                                                                                                                                                                                                                                                      |
| Cumulative CO exposure over 12 months              | Expired CO will be measured at each follow-up visit allowing an assessment of cumulative CO exposure. (baseline, Mo 3, 6 & 12)                                                                                                                                       |
| NNAL exposure over 12 months                       | Urinary NNAL will be measured at each follow-up visit allowing an assessment of cumulative NNAL exposure. (baseline, Mo 3, 6 & 12)                                                                                                                                   |
| Clinical outcomes                                  |                                                                                                                                                                                                                                                                      |

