### Analytical Plan.

**Sample Size and Power Calculations.** Our sample size was based on our primary outcome, point-prevalence abstinence at Month 12, using an intent-to-treat approach. Based on prior studies using precessation NRT, we estimate a 2-fold increase in cessation outcomes in the LT-NRT group compared to the SSC group. Given our recruitment of patients at all levels of readiness to quit, we estimate a 12 month cessation rate of 10%. With 199 participants, in each arm, we will have an 80% power to detect a 2-fold difference or greater with a Type I error rate of 5%. This sample size will provide comparable power for looking at 6 month sustained cessation. For the CO measured longitudinally at four time points, we have 80% power to detect a mean difference of 2.24 ppm. Likewise, for NNAL, we have 80% power to detect a mean difference of 0.41 pmol/mg creatinine or more between the two groups.

**Specific Aim 1: Compare the benefits of traditional smoking cessation (SSC) versus long-term guided maintenance therapy (LT-NRT) with NRT.** The chi-square test will be used to compare the verified 7-day point prevalence abstinence at Month 12 between the two groups. If there is imbalance between treatment groups at baseline, we will switch to logistic regression for our primary analysis. We will use similar methods to test for group differences for dichotomous secondary outcomes including sustained abstinence and proportion with 1 or more ED visits or hospitalizations. To test for differences in change in respiratory symptoms and FEV1 from baseline measured at 3, 6, and 12 months, we will use standard mixed models repeated measures analysis. Likewise, to test for differences in longitudinal exposure to CO and NNAL, we will compare the area under the curve over the entire 12 months of follow-up using repeated measures analysis. If the treatment differences are heterogeneous across any covariate sub-groups, we will quantify and report such interactions

with appropriate contrast statements. We will compare the cumulative number of self-reported quit attempts by means of a Wilcoxon rank-sum test.

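### The CO and NNAL power statement counts the pre-treatment baseline as one of four time points, and the 12-month AUC comparison states no baseline adjustment; making baseline a covariate is a free gain in precision

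*Protocol*

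**What the plan says.** The sample size paragraph of the Analytical Plan sets the trial size on abstinence: "With 199 participants, in each arm, we will have an 80% power to detect a 2-fold difference or greater with a Type I error rate". The rate it names is 5%. For smoke exposure the paragraph adds "For the CO measured longitudinally at four time points, we have 80% power to detect a mean difference of 2.24 ppm", and it gives a matching statement on the second marker: "for NNAL, we have 80% power to detect a mean difference of 0.41 pmol/mg creatinine or more between the two groups".

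Table 4 (Measures) gives the schedule. For CO: "Expired CO will be measured at each follow-up visit allowing an assessment of cumulative CO exposure. (baseline, Mo 3, 6 & 12"). For NNAL: "Urinary NNAL will be measured at each follow-up visit allowing an assessment of cumulative NNAL exposure. (baseline, Mo 3, 6 & 12"). The Study design section gives three outcome assessments after randomisation, at 3, 6 and 12 months. The description of the LT-NRT arm has NRT starting straight after the baseline visit.

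For the analysis of CO and NNAL, Specific Aim 1 says: "we will compare the area under the curve over the entire 12 months of follow-up using repeated measures analysis". It does not say whether baseline is a covariate, is subtracted, or is one of the responses. Table 5, which lists covariates, names baseline FEV1 and CAT score but neither CO nor NNAL. The SD, the within-person correlation and the power formula behind 2.24 and 0.41 are not given.

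**The concern.** Four time points can only mean baseline plus the three follow-up visits. At baseline the expected difference between randomised arms is zero. If the baseline value is handled as an ordinary response, it pulls the estimated difference towards zero. An AUC covering all 12 months would normally start from the month-0 value, because the first follow-up value comes at month 3.

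The same baseline value used as a covariate helps instead, since a person's baseline exposure predicts later exposure. The wording therefore leaves open two analyses whose power differs considerably. CO and NNAL are the protocol's objective measures of smoke exposure, preferred to self-reported cigarettes per day and to cotinine. A null result from a diluted comparison could be misread as no reduction in exposure.

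**Working it through.** **Inputs from the protocol.** 199 per arm; 80% power; type I error 5% (sidedness not stated, two-sided assumed, and assumed to carry over to CO and NNAL); detectable differences 2.24 ppm and 0.41 pmol/mg; visits at months 0, 3, 6 and 12.

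**Inputs assumed.** Correlation 0.3 to 0.9, as compound symmetry or as serial decay per 3 months; a constant difference after baseline; no missing data.

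**1. Primary sample size.** For 10% v 20%, the mean rate is 0.15 and n = [1.96·√(2·0.15·0.85) + 0.842·√(0.10·0.90 + 0.20·0.80)]² / 0.10² = (0.990 + 0.421)² / 0.01 ≈ 199. The stated size reproduces, with power 80.0%, which supports reading the 5% as two-sided.

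**2. The CO and NNAL figures.** Detectable difference = (1.960 + 0.842)·√(2/199)·SD = 0.2809·SD, where SD is that of the per-person summary. Inverting gives 2.24/0.2809 = 7.98 ppm and 0.41/0.2809 = 1.46 pmol/mg. Neither can be checked against the protocol, so the stated figures can be inverted but not reproduced.

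**3. Dilution.** Trapezoid weights for months 0, 3, 6 and 12 are 1.5, 3, 4.5 and 3, each over 12: 0.125, 0.25, 0.375 and 0.25. Baseline carries 12.5%, so a constant post-baseline difference is multiplied by 0.875. In an equally weighted four-visit mean the multiplier is 0.75. Neither multiplier depends on SD or correlation.

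**4. Consequence, if 2.24 ppm belongs to an equally weighted four-visit mean.** Under compound symmetry with correlation ρ, the per-visit SD is 7.98/√((1+3ρ)/4). At ρ = 0.5 it is 10.09 ppm.

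- Unadjusted AUC: variance factor = (1−ρ)·0.28125 + ρ = 0.6406 at ρ = 0.5. Detectable difference = 0.2809·10.09·√0.6406/0.875 = 2.59 ppm.
- AUC adjusted for baseline: subtract (0.125 + 0.875ρ)² = 0.3164, leaving 0.3242. Detectable difference = 0.2809·10.09·√0.3242/0.875 = 1.84 ppm.

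| Correlation | Per-visit SD (ppm) | Unadjusted AUC: detectable (power at 2.24) | Adjusted AUC: detectable (power at 2.24) |
|---|---|---|---|
| Compound symmetry 0.3 | 11.57 | 2.62 (66.9%) | 2.19 (81.8%) |
| Compound symmetry 0.5 | 10.09 | 2.59 (67.8%) | 1.84 (92.6%) |
| Compound symmetry 0.7 | 9.06 | 2.58 (68.3%) | 1.43 (99.3%) |
| Compound symmetry 0.9 | 8.29 | 2.56 (68.7%) | 0.82 (>99%) |
| Serial decay 0.3 | 13.44 | 2.68 (64.9%) | 2.48 (71.6%) |
| Serial decay 0.5 | 11.75 | 2.66 (65.7%) | 2.28 (78.5%) |
| Serial decay 0.7 | 10.13 | 2.62 (66.7%) | 1.94 (89.9%) |

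NNAL scales by 0.41/2.24 = 0.183. The unadjusted AUC range of 2.56-2.68 ppm becomes 0.47-0.49 pmol/mg.

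**5. Does baseline have to leave the AUC?** No. The adjusted 0-12 month AUC and the adjusted mean of the three follow-up visits differ by at most 0.07 ppm in detectable difference over all correlations tried (2.48 v 2.41 at serial decay 0.3).

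**The case against.** A reader might infer that 2.24 ppm and 0.41 pmol/mg are simply too favourable and that power is overstated. The protocol does not support that. With no SD, correlation or formula, step 4 back-solves the SD by supposing that the figure came from an unadjusted four-visit mean, which is the very treatment of baseline in question. If the stated mean difference is defined on the four-visit average itself, the number may be internally correct, though it is not the effect after treatment starts. The corresponding result for an equally weighted mean (2.24/0.75 = 2.99 ppm; NNAL 0.41/0.75 = 0.55) does not describe the planned AUC.

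Nor does the text rule out adjustment. The AUC sentence follows directly on one about change from baseline, and a longitudinal model may legitimately include baseline among the responses if its mean is constrained equal across arms. With adjustment, the stated figures could be conservative at every compound-symmetry correlation tried. Covariates can also reasonably be left to an analysis plan.

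A second tempting inference is that baseline should be dropped from the exposure measure. Table 4 defines the outcome over 12 months, and an AUC of months 3 to 12 would discard the first three months of it.

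What stands is narrower. The protocol itself fixes the count of time points, the detectable differences and the AUC window, and together these leave unclear which effect the power statement describes.

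**Conclusion.** The concern holds in a conditional form. It is certain from the protocol that one of the four time points precedes treatment, and that no baseline adjustment is stated for the CO and NNAL comparison. That the AUC starts at month 0 is an inference from its 12-month window.

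If baseline is an unadjusted response, the AUC contrast is diluted by one eighth. If in addition the stated figures belong to an equally weighted four-visit mean, 80% power needs about 14-20% more than stated (2.56/2.24 = 1.14; 2.68/2.24 = 1.20). These sizes rest on a constant post-baseline difference, complete data and the assumed correlations.

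The recommendation does not depend on which reading is right. Adjustment lowered the detectable difference at every correlation tried, though the gain is small under serial decay at low correlation (2.68 to 2.48 ppm at 0.3), where power at 2.24 ppm stays below 80%. CO and NNAL are secondary outcomes. The 199 per arm and the primary test are unaffected, so this is a worthwhile improvement and not a threat to the trial.

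**What to change.** - Keep the 0-12 month AUC as the exposure measure. State that it is compared between arms with baseline CO (or NNAL) as a covariate, or through a longitudinal model in which the baseline means are constrained equal across arms.
- Reword the power statement as three post-randomisation visits with baseline adjustment, say that the difference meant is the one after randomisation, and give the SD and correlation used for each marker.
- Restate the detectable differences on that basis. For CO, under the assumptions in the working, illustrative values are 2.19, 1.84 and 1.43 ppm at correlations 0.3, 0.5 and 0.7 with compound symmetry, and up to 2.48 ppm with serial decay at low correlation. The final figures need the investigators' own SD and correlation.

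The cost is a change of wording and one recalculation. Baseline CO and NNAL are already collected, and no visit, assay or participant is added.

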### Randomization

All eligible participants who consent to participate in the study and complete the baseline data collection will be randomized to either SSC or LT-NRT. Randomization will be determined by computer-generated random numbers and a randomization module embedded in the data capture program.

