### Intervention

Both intervention arms will receive written smoking cessation materials and a series of 4 telephone-based counseling sessions and 1-3 in-person counseling sessions. Although the number, timing, and content of the counseling sessions will differ across the treatment arms, we anticipate that the total counseling contact time will be comparable, with one caveat. Participants in the SSC arm who are not interested in quitting within 30 days at the time of their baseline counseling session will not be offered additional counseling, which is consistent with most state quitlines. These participants will be informed that they may contact the program's hotline if they change their mind, at which point, counseling may either be reinstated or they will be referred to the state quit line for counseling. Participants in the SSC arm will receive 10 weeks of NRT contingent upon setting a quit date while participants in the LT-NRT arm will receive 52 weeks of NRT regardless of their immediate interest in quitting. An overview of the interventions is shown in Table 2.

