## Measures

**Outcome measures.** Our selection of outcomes was derived from scientific expert consensus and informed by input from our stakeholders and smokers with COPD. (Table 4) The primary outcome is biochemically verified 7-day point prevalence smoking abstinence defined as no cigarettes (not even a puff) for the previous 7 days at month 12. Biochemical validation will be based on expired CO, consistent with consensus statements from the Society for Research on Nicotine and Tobacco (SRNT). For those participants who have reported they have quit smoking and who are unable to be verified in this way, we will obtain verbal permission and contact information for a household member or other regular contact to provide proxy validation.

Secondary outcomes are 6 month sustained abstinence (biochemically verified), number of quit attempts, average CPD over the year of the study, and cumulative exposure to CO and NNAL. We will examine relapse rates 3 months after the conclusion of the study for participants who report they have quit smoking at the 12-month assessment. Clinical outcomes include both objective and subjective measures of respiratory function based on the measured FEV1 (as a percent of predicted) and the COPD Assessment Test.

We will also track both respiratory and cardiac clinical events. This will be done by self-report of intercurrent emergency department visits and hospitalizations at each follow-up visit. We will validate both the occurrence and the nature of these self-reported clinical events by blinded physician review of medical records.

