### Covariates

We will collect a variety of covariates (Table 5). These covariates will allow us to verify the comparability of the two comparison arms at baseline and will also allow us to estimate treatment effects for given personal characteristics (see discussion of CART analysis in the analytic plan). We will assess demographic variables, social history variables that might influence tobacco consumption, smoking related variables, including cpd, nicotine dependence, and biological markers of nicotine consumption, and clinical variables including both objective and subjective assessment of respiratory function and prior history of respiratory-related clinical events.

| Table 5. Co-variate measures |                                                                                                                                                                                  |
|------------------------------|----------------------------------------------------------------------------------------------------------------------------------------------------------------------------------|
| Construct                    | Measure (assessment timepoint)                                                                                                                                                   |
| Demographics                 | gender, age, race, ethnicity, income, education, employment, marital status, family structure (baseline)                                                                         |
| Social history               | Other smokers in the home, presence of home smoking restrictions, anxiety (GAD-2), depression (PHQ-2), health history (baseline)                                                 |
| Smoking Variables            |                                                                                                                                                                                  |
| Smoking history              | Quantity smoked (baseline, Mo 3, 6 & 12), quitting history, use of other tobacco and nicotine products, including e-cigs and NRT, (baseline)                                     |
| Readiness to quit            | Interest in quitting will be assessed using 30 day anchor (stage of change) and 12 months (intent to cut back or quit) (baseline, Mo 3, 6 and 12)                                |

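### The primary analysis depends on observed baseline balance (chi-square, or logistic regression if the arms look imbalanced) and should be one analysis fixed in advance

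*Protocol*

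**What the plan says.** The Measures section defines a binary primary outcome, biochemically verified 7-day point prevalence abstinence at month 12. Under Specific Aim 1 the Analytical Plan sets the default: "The chi-square test will be used to compare the verified 7-day point prevalence abstinence at Month 12 between the two groups". The next sentence makes that default conditional: "If there is imbalance between treatment groups at baseline, we will switch to logistic regression for our primary analysis". The text gives no threshold for imbalance, no list of variables to be checked and no set of covariates for the logistic model.

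The plan then reads as extending the same approach to other endpoints: "We will use similar methods to test for group differences for dichotomous secondary outcomes including sustained abstinence", along with the proportion having an ED visit or hospitalization.

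The Covariates section, which introduces Table 5, gives the balance check its source: "These covariates will allow us to verify the comparability of the two comparison arms at baseline". The Randomization section describes computer-generated allocation and mentions no stratification factors.

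**The concern.** The protocol names two primary analyses and lets the trial's data choose between them. That is awkward for three reasons.

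- **Wrong criterion.** Allocation is random, so any baseline difference is chance. A covariate belongs in the model because it is expected to predict abstinence, and that can be decided before enrolment.
- **Unsettled estimand.** A chi-square test compares crude proportions. A covariate-adjusted logistic model gives a conditional odds ratio, which differs from the crude one even in a perfectly balanced trial when the covariates are prognostic. Chance would decide which effect is reported.
- **Room for dispute.** With trigger and adjustment set open, a borderline result could be questioned on how the analysis was chosen.

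At stake are the credibility of the primary result and some precision. Readiness to quit, nicotine dependence (FTND) and cigarettes per day are all collected at baseline, but the default test uses none of them.

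**Working it through.** **1. The plan's own sample size.** Inputs from the Analytical Plan: 10% abstinence (read as the SSC rate), a 2-fold effect (so 20% in LT-NRT), 5% type I error (two-sided assumed), 80% power. With pooled variance and no continuity correction:

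n = [1.960·√(2·0.15·0.85) + 0.842·√(0.10·0.90 + 0.20·0.80)]² / 0.10² = (0.990 + 0.421)² / 0.01 ≈ 199 per arm.

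This reproduces the stated 199 (power 0.8001). The sample size therefore rests on the unadjusted chi-square.

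**2. The effect measures at those values.** Risk difference 20% − 10% = 10 points; risk ratio 2.0; crude odds ratio (0.20/0.80)/(0.10/0.90) = 2.25. A covariate-conditional odds ratio would be a further, different quantity.

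**3. How often the switch would occur.** The protocol gives no trigger, so this cannot be computed from it. As an assumption, let imbalance mean p<0.05 on any of k independent covariates. The chance is then 1 − 0.95^k:

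| k | 5 | 10 | 15 | 20 | 25 |
|---|---|---|---|---|---|
| Switch | 23% | 40% | 54% | 64% | 72% |

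Table 5 holds about 25 baseline items by our count.

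**4. Error and power of the rule.** Simulation with 199 per arm and 6,000 trials per scenario (4,000 for k = 15). Assumptions: k independent normal covariates with equal log odds ratio β per SD; the switch occurs if any has p<0.05, and the model then adjusts for the imbalanced ones only. Fixed adjustment always includes all k. Null is 10% v 10%; power is at 10% v 20%.

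| k, β | Null: chi-square / fixed / switching | Power: chi-square / fixed / switching |
|---|---|---|
| 1, 0.5 | 5.0 / 4.8 / 5.0% | 80.4 / 80.9 / 80.6% |
| 1, 1.0 | 4.7 / 4.7 / 4.5% | 80.0 / 84.2 / 80.4% |
| 5, 0.3 | 4.8 / 4.6 / 4.6% | 80.6 / 82.4 / 80.7% |
| 5, 0.5 | 4.9 / 5.2 / 4.6% | 80.7 / 85.3 / 80.7% |
| 15, 0.2 | 5.2 / 5.7 / 4.8% | 80.2 / 82.1 / 80.1% |

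Switching lost 0.3 to 4.6 points of power against fixed adjustment. The loss grows with total prognostic strength: the SD of the combined covariate score is β√k, and at 0.50, 0.67, 0.77, 1.00 and 1.12 the losses are 0.3, 1.7, 2.0, 3.7 and 4.6 points. The switching verdict differed from the chi-square in 0.3% to 2.6% of trials. Taking the better of the two p-values gave 4.8% to 5.4% error under the null.

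**5. Readiness to quit as the covariate.** Assumptions: one third ready to quit (in line with 7 of 21 in the sponsor's interviews), and SSC quit rates of 20% if ready and 5% if not (average ⅓·20% + ⅔·5% = 10%).

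- Risk ratio 2 in both groups, 6,000 trials: chi-square 80.8%, switching on readiness imbalance 81.3%, readiness-stratified test 83.7%. Null rates were 5.1%, 5.1% and 5.5%.
- Same scenario, 40,000 trials: stratified 84.4%, chi-square 81.3%.
- Weaker split, 14% v 8%, risk ratio 2: 81.0% v 80.8%.
- Benefit only in smokers not ready to quit (20%/5% becoming 20%/20%): 81.2% v 80.7%.
- Logistic model with readiness and two non-prognostic covariates: 83.8% against 81.5% for the chi-square in the first scenario, no gain in the other two.

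**6. Room for covariates.** Expected events: 398·0.10 ≈ 40 under the null; 199·0.10 + 199·0.20 ≈ 60 under the alternative. The highest null rate for fixed adjustment (5.7%) came with 15 covariates, so the list should be short.

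**The case against.** The best defence is that little goes wrong in practice. The trigger looks at baseline data and not at outcomes, type I error stays at about 5%, and the default test matches the sample-size calculation. The definition of imbalance and the covariate list are details that a statistical analysis plan commonly fixes, and that document was not available here. All of this stands and limits the severity. It does not remove the point: a later document could define the trigger, but the choice of primary analysis would still depend on the data.

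Stronger readings are tempting, and the protocol does not support them.

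- **That a switch is more likely than not.** This needs an any-covariate p<0.05 rule and independent covariates. The protocol states no such rule, and several Table 5 items are plausibly correlated (quantity smoked, FTND, cotinine; income, education).
- **That the rule inflates type I error.** The mechanical rule does not. In a worst-case simulation (20 independent covariates, 1,500 null trials, SE 0.6 to 0.7 points) an analyst picked the best p-value over subsets of up to six imbalanced covariates or the chi-square. Error was about 5% when imbalance meant p<0.05 and about 8% when it meant p<0.20. Nothing in the protocol plans such a search.
- **That readiness is overlooked, or that the treatment rules prove it prognostic.** In the SSC arm, "Participants in the SSC arm will receive 10 weeks of NRT contingent upon setting a quit date". That link exists in one arm only, so it suggests a differing treatment effect as much as a shared prognostic one. The protocol does plan to examine effect by readiness, through subgroup contrasts and the CART analysis.

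A fixed unadjusted chi-square would also cure the data-dependence, so adjustment is a preference with a modest gain.

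**Conclusion.** The point holds as a should-fix. The protocol states a rule under which observed baseline balance selects the primary analysis, and it appears to carry that rule to the dichotomous secondary outcomes. This is a poor criterion under randomisation, and it leaves the adjustment set and estimand open until trial data are seen.

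The numerical harm is modest: type I error 4.5% to 5.1% under mechanical use, and power about 0 to 3 points below fixed adjustment in most scenarios, up to 5 with very strong predictors. These figures rest on assumed covariate effects, assumed quit rates by readiness and assumed triggers, none of which the protocol gives. The planned 199 per arm is correct for the chi-square and is not challenged.

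**What to change.** Delete the switching sentence and name one primary analysis in advance. Preferably:

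- logistic regression of month-12 verified abstinence on arm, with a short pre-named list of baseline covariates already in Table 5, for example readiness to quit, FTND and cigarettes per day;
- a standardised risk difference and risk ratio, each with a 95% confidence interval;
- the unadjusted chi-square as a sensitivity analysis;
- the same fixed approach for the dichotomous secondary outcomes.

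At a minimum, make the unadjusted chi-square the sole primary test and label any adjusted model supportive.

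The cost is wording only: no new data and no change in sample size. The one small downside of the preferred option is that the model needs a standardisation step to yield the risk difference.
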